### Data collection

#### Baseline survey

Consented HCPs will complete an interviewer-administered electronic questionnaire using the Open Data Kit software to record participants’ characteristics and details on ADR reporting. Details of the questionnaires are provided in (online supplemental file 2).

10.1136/bmjopen-2022-061725.supp2Supplementary data

#### Mobile app data

The app is hosted by NDA where the NPC is located, which is also the preferred source of ADR risk information for users of the mobile app. HCPs with smartphones will submit reports that capture details on patient sociodemographics, suspected medicine, other concurrent medicines, suspected ADR and medical history. The NPC transmits alerts via the mobile app on emerging medication safety issues to users of the app.

#### Paper form and web form

The paper form and web form details will be distributed at all enrolled cART-sites. PV focal persons based at the cART-sites and NDA regulatory officers will routinely collect the paper forms and forward them to NPC for data capture in the national PV database and central analysis, prior to onward submission to the WHO database, VigiBase. HCPs also have the option to submit online ADR reports using the web form.

#### Economic cost data

Cost data will be collected by an appropriately trained RA. We will collect *setup costs* such as app development costs, equipment costs, cost of vehicles and training costs, and *running costs* such as airtime, internet data, app maintenance, personnel costs, buildings and space if any, transport (fuel), stationary, brochures, costs of registers and airtime/reminders. Both *setup* and *1-year running costs* will be collected from the provider perspective.

#### Feasibility and acceptability of the app

Prior to trial implementation, we will conduct a baseline qualitative study to gauge the acceptability and feasibility of introducing the app to HCPs. We will conduct three to five focus group discussions each with five to eight HCPs and 20–30 in-depth interviews in a random 6% of cART-sites (~12) in the intervention arm. During trial implementation, we will document the refusal and failure rates to instal the app among consented HCPs in the intervention arm. App users will be asked to report their experiences to gauge app feasibility, assess user satisfaction and identify potential revisions to the app. We will gauge acceptability of the app based on whether users can recommend the app to other HCPs to report suspected ADRs to NPC.

### Data management

#### Training of research assistants

Both the initial and ongoing trainings focus on the key concepts of PV, good clinical practice, human subject protection, randomisation, risk profiles of cART and IPT and techniques for collecting high-quality survey data among others.

#### Data quality assurance

The PV database quality manager at NDA will be trained and empowered by the research team to embed data quality management in the national PV database.

#### Data protection

All ADR data are processed and securely stored by NPC. Paper forms are manually entered into the PV database by authorised NPC staff, while online data are electronically transmitted into VigiFlow and assessed before transfer into VigiBase. Researchers can request anonymised safety data for research purposes only. Paper-based questionnaires are stored under lock and key and accessed only by authorised project staff. Electronic data are password protected and used for research purposes only. Data will be delinked from HCP identifiers prior to analysis.

#### Compliance with allocation

Prior to data anonymisation, an NPC officer not involved in the routine assessment of submitted ADR reports will code these reports according to the allocated trial arm of the site where the report originates. Our team will use the codes to assess the extent of cross-over.

### Data analysis

#### Success of randomisation

Baseline characteristics (sociodemographics of HCPs, pattern of smartphone ownership by HCPs at cART sites, geographical location of cART-site, nature and level of health facility, number and cadres of HCPs, number of PLHIV and use of DTG and IPT) will be compared in both study arms to establish if randomisation was successful.

#### Quantitative data

Analysis of results will be reported according to Consolidated Standards of Reporting Trials guidelines and performed on both intention-to-treat and per protocol bases. All ADR data received from the ~382 cART sites during the study period will be downloaded from VigiBase and anonymised by the PV manager at NPC and subsequently provided to the research team. Duplicate ADR reports will be identified and excluded from formal statistical analyses. The randomisation code will be broken after data analysis.

#### Unit of analysis

This unit will be an ADR site in keeping with the cluster-randomised design.

#### Analysis of missing or lost clusters

We will compare baseline characteristics of individuals in the lost clusters with the characteristics of individuals in the clusters that will have completed follow-up. If we find no significant differences between the clusters, we will conclude that our results do not include any differential misclassification. If there are differences, however, we will report this finding and discuss its implications.

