#### Sample size

To estimate the number of cART sites required per arm for an effect size of 25%,^26^ we assume power of 80% at the 95% confidence level, mean of 1.0 IPT-linked ADR/month/100 000 treated PLHIV (0.00001) and SD of 1.179 IPT-linked ADRs/month/100 000 treated PLHIV (0.00001179) (SD was computed based on the monthly IPT-linked ADR reports submitted to NPC for 1 year from October 2018 to September 2019), cluster size of 10 HCPs and coefficient of variation of 0.25,^26^ which yields ~114 cART sites per trial arm or 228 in both study arms. A minimum of 189 cART sites per arm or 378 in both study arms (66% increment) will be required to cater for the following limitations: (1) the large proportion of HCPs who do not own smartphones of ~50%–60% as previously estimated^21 22^ – and is 26% (95% CI of 23% to 30%) from limited rollout of RCT; (2) refusal to participate by eligible HCPs of ~5% as previously estimated^27^ – and is 0% (95% CI of 0% to 2%) from limited rollout of RCT; (3) loss to follow-up due to the relatively long follow-up period of 30 months (~10%); and (4) contamination due to information sharing between study arms through social media (~30%).^28^ We shall enrol 382 cART sites (191 per study arm) to cater for other unforeseen limitations; thus, recruiting up to 3820 HCPs (1910 HCPs per trial arm). Limited rollout of the RCT suggests a cluster size of 7.2 (629/87) HCPs. We shall retain the average cluster size of 10 HCPs because the RCT has not yet enrolled from the central region of Uganda (with the country’s capital city) where cART sites tend to be much larger with more HCPs per site than the more rural eastern, western and northern regions.

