#### Effectiveness

Descriptive data will be aggregated to obtain the number of HCP-reported ADRs per 100 000 treated PLHIV per trial arm and compared at cluster level using the Student’s t-test or Wilcoxon rank-sum test, as appropriate, to determine if the app significantly increases ADR reporting. We will assess if the introduction of Med Safety increases the rate of ADR reporting by HCPs to NPC versus the use of existing PV methods (paper and online) alone during 30 months of follow-up and effect size of 25% at 5% level of statistical significance and power of 80%.

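### A non-significant, arm-pooled baseline comparison of lost and completed clusters is taken as proof of no differential misclassification, an inference it cannot support

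*Protocol article*

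**What the plan says.** The rule is in the protocol article, under Analysis of missing or lost clusters. It first describes the comparison: "We will compare baseline characteristics of individuals in the lost clusters with the characteristics of individuals in the clusters that will have completed follow-up". The two outcomes of that comparison then lead to two actions. If nothing is significant: "If we find no significant differences between the clusters, we will conclude that our results do not include any differential misclassification". If something is: "If there are differences, however, we will report this finding and discuss its implications". No margin for an acceptable difference is given, and the comparison is not split by arm.

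Three other places bear on it:

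- **Sample size** lists, among the reasons for inflating the number of sites, "loss to follow-up due to the relatively long follow-up period of 30 months (~10" percent), without saying whether sites or healthcare professionals (HCPs) are meant. It sets enrolment at 382 sites, 191 per arm.
- **Quantitative data** commits to both intention-to-treat and per-protocol analyses, and to obtaining all adverse drug reaction (ADR) reports received from the roughly 382 sites from VigiBase.
- **Paper form and web form** says that site focal persons and regulatory officers "will routinely collect the paper forms and forward them to NPC for data capture in the national PV database and central analysis". Web reports are a further option.

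**The concern.** The rule fixes in advance a favourable statement about the validity of the results, and the evidence that triggers it cannot carry that statement. Four faults are separate from any question of power:

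1. Failing to reject a null hypothesis does not establish it. Without a margin, the rule rewards imprecision: the fewer clusters are lost, the easier it is to find nothing.
2. The effect of the app is a contrast between arms. It is biased when loss differs between arms in amount or in kind. A comparison of lost with completed clusters over both arms together does not look at that.
3. The primary outcome is the ADR reporting rate. Similar baseline characteristics do not show that the unseen reporting rates of lost sites resemble those of the rest.
4. Losing clusters raises attrition (selection) bias. Misclassification is an error in how outcomes or exposures are recorded, and this comparison does not address it.

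The other branch is also weak: if differences appear, they are only reported and discussed. At stake is an unsupported validity claim attached to the main result, made by following the plan exactly.

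**Working it through.** **The plan's own figure.** The article states no number of lost sites and no power for this comparison, so there is nothing to reproduce. The inputs are 382 sites, ~10% loss and 10 HCPs per site (7.2 seen in the limited rollout), all from Sample size. A two-sided 5% level is taken from the same section's 95% confidence level.

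**Assumption on the unit of loss.** Read as sites, 0.10 × 382 = 38 lost and 382 − 38 = 344 retained.

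**Pooling the arms.** Suppose 19 sites are lost per arm and a trait is present in 50% of retained sites. If it is present in 70% of lost intervention sites and 30% of lost comparison sites, the pooled figure for lost sites is (0.70 + 0.30)/2 = 50%. The planned comparison then shows no difference at all, although loss is strongly selective in opposite directions. This example is constructed to show the mechanism; nothing in the article predicts it.

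**Power for a site-level trait** (for example facility level or location). Normal approximation for two proportions: power = Φ[(|p1 − p2| − 1.96 × SE0)/SE1]. SE1 is the unpooled standard error; SE0 is either pooled or unpooled, which gives the small ranges below.

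- 60% vs 50%, 38 vs 344: SE1 = √(0.24/38 + 0.25/344) = 0.0839. Unpooled: 0.10/0.0839 − 1.96 = −0.77, so power is 22%. Pooled: 21%.
- 70% vs 50%, 38 vs 344: 66–72%.
- Continuous trait: SE = √(1/38 + 1/344) = 0.171 SD. Power for a 0.3 SD difference is Φ(0.3/0.171 − 1.96) = 42%. The 95% confidence half-width is 1.96 × 0.171 = 0.34 SD.

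Range over the assumed share of sites lost:

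| Loss | Sites lost | Power, 60% vs 50% | Power, 0.3 SD |
|---|---|---|---|
| 5% | 19 | 13–14% | 25% |
| 10% | 38 | 21–22% | 42% |
| 15% | 57 | 28–29% | 55% |
| 20% | 76 | 34–35% | 65% |

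**Power for an HCP-level trait.** The plan compares individuals, so this case matters. The effective number is sites × m/[1 + (m − 1) × ICC]. The intracluster correlations (ICCs) are assumptions. With m = 10 and 60% vs 50%:

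| ICC | Design effect | Effective lost / retained | Power |
|---|---|---|---|
| 0.01 | 1.09 | 349 / 3156 | 95% |
| 0.05 | 1.45 | 262 / 2372 | 87–88% |
| 0.10 | 1.90 | 200 / 1811 | 77–78% |
| 0.25 | 3.25 | 117 / 1058 | 54–55% |

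With 7.2 HCPs per site the range is about 50–87%.

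**A test by arm would not rescue the rule.** With 19 lost and 172 retained per arm (assumed), the standard error for the difference between arms in the lost-minus-retained contrast is √[2 × (1/19 + 1/172)] = 0.342 SD. Power for 0.3 SD is Φ(0.3/0.342 − 1.96) = 14%. Estimates with intervals are therefore more useful than another significance test.

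**What selective loss could do, as an illustration only.** Assume no true effect, 10% of intervention sites lost, no selective loss in the comparison arm, and lost sites left out. If lost sites report at a fraction r of the average rate, the completers-only rate ratio is (1 − 0.1r)/0.9:

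- r = 0: 1/0.9 = 1.11, an apparent gain equal to 0.11/0.25 = 44% of the 25% target.
- r = 0.5: 0.95/0.9 = 1.06.
- The same selective loss in both arms: ratio 1.0.

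**The case against.** The strongest reply has four parts.

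- **Power.** The plan compares individuals, not sites. For HCP traits with modest clustering, the comparison is reasonably powered. This stands: low power cannot be the main argument, and it would be wrong to say that the rule fails simply because about 38 sites are too few. Moreover, 38 is not in the article; the ~10% has no unit and sits beside two HCP-level items (smartphone ownership and refusal), so it may mean HCPs.
- **Wording.** A reader might infer that the trial will declare its results free of bias. The text is narrower: it speaks only of differential misclassification. The term is the wrong one for lost clusters, but the wider claim should not be attributed to the plan.
- **Analysis set.** A reader might infer a completers-only primary analysis. The article does not state one. Quantitative data promises intention-to-treat and all reports from the roughly 382 sites, and a site that sends nothing can then count as zero reports. The ratios of 1.11 and 1.06 need one-sided selective loss and exclusion of lost sites, neither of which the article states.
- **Level of detail.** Sensitivity analyses are often left to a statistical analysis plan. That is fair, and their absence is not the fault raised here. The fault is an inference that the article states.

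None of this repairs the inference. Even a well-powered comparison of individuals would pool the arms, would say nothing about unobserved reporting rates, and would address the wrong kind of bias. No other section of the article tempers the rule.

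**Conclusion.** The rule is wrong as written and should be changed before the data are analysed. The conclusion rests on the logic of the stated rule and needs no numerical assumption.

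The figures are secondary. Power of about 21–22% (60% vs 50%) applies only to site-level traits and only if ~10% means sites. For HCP-level traits, power is about 54–95% under the assumed ICCs with 10 HCPs per site. If fewer sites are lost, the test is weaker, but the possible bias is smaller too.

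The documents do not show that the primary estimate will be biased. The rule does not alter the outcome, the test or the data set; it governs what will be claimed about them. The article does leave unclear whether a lost cluster stays in the intention-to-treat analysis, and that should be settled in the same edit.

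**What to change.** Under Analysis of missing or lost clusters:

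1. Delete the conclusion drawn from non-significance, and name the concern as attrition (selection) bias.
2. Define a lost cluster, and report the number lost by arm with reasons. Describe lost and retained sites within each arm by standardised differences with confidence intervals, not by significance tests. Coded arm labels would keep the analyst blinded.
3. State that lost clusters stay in the intention-to-treat analysis of all 382 randomised sites, using the reports that reach the National Pharmacovigilance Centre and VigiBase whether or not the enrolled HCPs are still followed.
4. For any site whose reports or person-months of treated patients are truly unavailable, add a simple sensitivity analysis by arm. For example, give such sites the comparison-arm rate and, as the case least favourable to the app, zero further reports in the intervention arm only.

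The cost is a few sentences and slightly more analysis work. The reports already flow to the national database; the one extra need is to keep collecting each site's treated-patient denominator after its HCPs leave follow-up.

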#### Descriptive statistics

We shall determine the frequencies of deduplicated HCP-reported ADRs per 100 000 treated PLHIV per cART site together with the time from ADR onset to VigiBase registration.^29^

#### Effectiveness

Descriptive data will be aggregated to obtain the number of HCP-reported ADRs per 100 000 treated PLHIV per trial arm and compared at cluster level using the Student’s t-test or Wilcoxon rank-sum test, as appropriate, to determine if the app significantly increases ADR reporting. We will assess if the introduction of Med Safety increases the rate of ADR reporting by HCPs to NPC versus the use of existing PV methods (paper and online) alone during 30 months of follow-up and effect size of 25% at 5% level of statistical significance and power of 80%.

#### Multivariable analysis

Models will use the number of ADR reports as the outcome. Hierarchical models (level 1: cART sites; level 2: HCPs nested within cART sites; level 3: individuals nested within HCPs) will be fitted using maximum log-likelihood, considering intracluster correlations, using mixed models and generalised estimating equations models to control for potential confounders and effect modifiers identified at baseline assessment if fair randomisation fails. Subgroup analyses will also be performed.

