#### Concealment of sequence generation

Using the sealed envelope software, an independent Biostatistician from the Clinical Epidemiology Unit at Makerere University, who will not participate in the subsequent data analyses, generated the simple randomisation sequence.

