#### Randomisation

The prescreened cART sites will be assigned by research assistants to the intervention and comparison arms, figure 2, using an electronically generated simple randomisation sequence.

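### Covariate adjustment hangs on a baseline check that cannot show failed randomisation, and the model named for it has a patient level the report data cannot support

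*Protocol article*

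**What the plan says.** All references are to the protocol article.

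- **Trigger.** Multivariable analysis proposes mixed models and generalised estimating equations for the number of ADR reports, "to control for potential confounders and effect modifiers identified at baseline assessment if fair randomisation fails".
- **How failure is judged.** Success of randomisation lists about seven groups of HCP and site characteristics (about ten single items). These "will be compared in both study arms to establish if randomisation was successful". No threshold or decision rule follows.
- **Allocation.** An independent biostatistician "generated the simple randomisation sequence", and sites are assigned "using an electronically generated simple randomisation sequence". No stratification or other restriction is stated.
- **Model levels.** Below the site, the model has "level 2: HCPs nested within cART sites; level 3: individuals nested within HCPs".
- **Data.** ADR reports are "downloaded from VigiBase and anonymised by the PV manager at NPC" (Quantitative data). Data protection adds: "Data will be delinked from HCP identifiers prior to analysis".
- **Denominator and unit.** Unit of randomisation says that using sites as clusters supplies the PLHIV denominators. Descriptive statistics computes rates per site. Unit of analysis is the site.
- **Main comparison.** Effectiveness sets an unadjusted cluster-level t-test or rank-sum test.

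**The concern.** There are two faults, both in what the text states.

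First, a baseline table cannot do the job given to it. If the sequence is sound, a difference between arms in region, facility level or PLHIV volume is a chance event whatever its size. Finding one does not show that randomisation failed, and finding none does not make adjustment useless. What makes a covariate worth including is its relation to reporting, not its imbalance. Effect modifiers cannot be identified from a baseline comparison at all. The rule therefore leaves the decision to adjust, and the choice of covariates, until the data are seen. Under simple randomisation, prognostic site features are not balanced by design, so planned adjustment is useful here.

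Second, the model has levels that the described data do not contain. The primary outcome is a rate over person-months of treated PLHIV. A patient level built from reports holds only patients who were reported on, so it cannot yield that rate.

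At stake are precision in the trial's main question and the clarity of the adjusted result. The validity of the unadjusted test is not in question.

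**Working it through.** **1. The plan's own sample size, used as the base for power.** Inputs from Sample size: difference 0.25 (25% of a mean of 1.0), SD 1.179, power 80%, 95% confidence (two-sided assumed), 10 HCPs per site, clustering parameter 0.25.

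- HCPs per arm: 2 × (1.960 + 0.842)² × 1.179² / 0.25² = 349.1, so 350.
- Design effect: 1 + (10 − 1) × 0.25 = 3.25.
- Sites per arm: 350 × 3.25 / 10 = 113.75, so 114. This matches the plan.
- With the 66% increment: 114 × 1.66 = 189. This also matches.

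The match requires 0.25 to act as an intracluster correlation, although the plan calls it a coefficient of variation. That is a separate matter; 114 serves here only as the point of 80% power.

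**2. How often chance alone could fire a trigger.** The plan gives no rule, so assume a 5% test on each item, independence, and that any one difference counts.

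- 7 comparisons: 1 − 0.95⁷ = 0.30.
- 10 comparisons: 1 − 0.95¹⁰ = 0.40.

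**3. Gain from adjusting always.** Let R² be the share of the variance of site rates that the covariates explain. The documents do not give it. Sites needed are 113.75 × (1 − R²). Power at 114 sites is Φ[2.802 × √(114/113.75) / √(1 − R²) − 1.960].

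| R² (assumed) | Sites per arm for 80% power | Power at 114 sites |
|---|---|---|
| 0 | 114 | 80% |
| 0.1 | 103 | 84% |
| 0.3 | 80 | 92% |
| 0.5 | 57 | 98% |

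**4. Triggered against planned adjustment, by simulation.** The set-up was 191 sites per arm, a normal site-level outcome, eight independent baseline covariates of which one is prognostic, an effect of 0.2867 SD (unadjusted power about 80%), and 6,000 runs per setting. Triggered means adjusting for whichever covariates differ at p<0.05. Planned means always adjusting for the prognostic one.

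| | R² 0.1 | R² 0.3 | R² 0.5 |
|---|---|---|---|
| Power, triggered | 80% | 80% | 82% |
| Power, planned | 84% | 91% | 98% |
| Type I error, triggered | 5.1% | 4.7% | 3.4% |
| Type I error, better of unadjusted and adjusted | 6.8% | 7.8% | 8.0% |

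The trigger fired in 33% to 34% of runs, yet it recovered almost none of the available power. Applied mechanically, it did not inflate type I error. The last row needs an analyst who reports whichever result is significant.

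**5. Model levels against the described data.**

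- *Site:* reports can be traced to the originating site (Compliance with allocation codes them by that site's arm), and denominators exist per site. This level is supported.
- *HCP:* enrolled HCPs consent and are surveyed, so a roster that includes non-reporters exists. Linking reports to it needs a code that survives delinking, and none is described.
- *Patient:* the extract holds reports only, and nothing attaches treated patients, or a count of them, to an individual HCP. Patients without a report are absent, so this level cannot estimate a reporting rate.

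**The case against.** The strongest reply is that the trigger touches only a supporting analysis. Effectiveness already fixes an unadjusted cluster-level comparison that does not depend on the baseline table and is valid for 382 randomised sites. This stands. A reader might infer that the primary estimate is undefined, or that chance decides which model is reported; the Effectiveness section rules that out.

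Second, the 30% to 40% figures rest on a test, a threshold, an any-one-differs rule and independence, none of which the protocol states. This also stands. Independence is doubtful for facility level, number of HCPs and number of PLHIV. The figures illustrate how a trigger could behave and do not describe a stated rule. A reader might likewise infer inflated type I error, but the mechanical trigger shows none. The 6.8% to 8.0% would require setting aside the comparison that Effectiveness names.

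Third, not every baseline difference need be chance. HCPs join by consent, the research assistants who assign sites are unblinded, and the article does not say that consent precedes allocation. Comparing HCP characteristics between arms therefore has a use. But a difference there would point to selective recruitment, not failed randomisation, so the stated purpose is still wrong.

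Fourth, removing HCP identifiers is ordinary data protection and does not exclude a study code. This stands: the documents do not support saying that the HCP level cannot be fitted.

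Fifth, a covariate list and model family are commonly left to an analysis plan. That is true of the details. The conditional rule and the patient level are written here, and a later plan would have to contradict this text to remove them.

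**Conclusion.** The point holds for the supporting adjusted analysis. The article makes adjustment conditional on a comparison that, for site features under a sound sequence, cannot answer the question put to it. It also names a patient level at odds with its reports-only extract, per-site denominators and site-level unit of analysis. The HCP level is unresolved rather than impossible.

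The main cost is lost precision. From a base of 80%, planned adjustment would give about 84%, 92% and 98% power at R² of 0.1, 0.3 and 0.5, while triggered adjustment stays at 80% to 82%. These figures assume the R² values, a normal site-level outcome and the plan's own variance inputs, so they show a range and do not forecast the gain. If the covariates explain little, the gain is small. The unadjusted comparison remains valid throughout. The change is worth making because it is cheap, not because the trial fails without it.

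**What to change.** - State in advance one adjusted site-level count model, for example negative binomial, with log person-months of treated PLHIV as offset. Use site characteristics already on the baseline list: geographical location, facility level and number of PLHIV. Fit it whatever the baseline table shows, and report it beside the unadjusted comparison in Effectiveness.
- Present baseline data descriptively and remove the aim of establishing whether randomisation succeeded. HCP characteristics may still be inspected for selective recruitment, if labelled so.
- Drop the patient level. Keep an HCP level only as secondary work, with a documented pseudonymous code that survives delinking.
- Add pre-trial ADR counts per site only if the NPC can supply them; the article does not say that it can. They may be sparse: the 109 DTG-linked reports in the Introduction, even if all came from these sites, average 109/382 = 0.29 per site.

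The first two changes are analysis wording on data already planned, with no added sites, participants or visits. A pseudonymous HCP code would need a small addition to the NPC's data handling, and only if HCP-level work is wanted.
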